### 3.4. Plasma hormonal determination

Plasma cortisol, insulin, leptin and thyroid free-T3 and T4 will be determined for AT analysis in 4 moments (Fig 1). Measurements of plasma thyroid levels (free-T3 and T4) and cortisol will be determined by immunoassay with chemiluminescence detection (Advia Centaur, Siemens). Insulin assessment will be performed in an automated analyser with chemiluminescence detection (Advia Centaur, Siemens), and leptin plasma levels by enzyme immunoassay (ELISA). Reference values for these parameters will be considered.

### 3.5. Statistics

Statistical analysis will be performed using SPSS statistics software version 29.0, 2022 (SPSS Inc., an IBM Company, Chicago IL, USA), with a statistical significance set at p<0.05 (2-tailed).

Descriptive statistics will be calculated (mean, standard deviation, and range). Linear mixed models will be used to assess outcomes for the impact of group, time and group*time interaction, including the randomized group (control vs intervention group) and time (baseline at the 2-week EB, at the start and every 4-week of ER intervention phase, at the start and at the end of the 8-week post-diet EB phase, and at the end of WM phase) as fixed effects. When necessary, adjustments for confounding variables (covariates) will be considered. The covariance matrix for repeated measures within subjects over time will be modelled as unstructured or, if necessary, compound symmetry. The normality of model residual distributions will be examined graphically and with the Kolmogorov-Smirnov test. Difference-in-differences between IER and CER throughout time will be assessed by performing contrasts [Difference-in-differences (DiD)], calculated as the difference between changes for IER (Difference_IER = T2 -T1) and changes for CER (Difference_CER = Time2 –Time1): DiD = (Difference_IER)–(Difference_CER).

All analysis will be intention-to-treat, including data from all the participants who will assign in this study. Sensitivity analyses will be carried out for some variables of interest, by using single imputation of missing data to predict missing outcomes from demographics and baseline measures.

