**Fig 1 pone.0294131.g001:**
[figure not shown]
SPIRIT diagram. *Time-points of the protocol: *-t*_*1*_, enrolment; *t*_*0*_, baseline; *t*_*2*_, 2 weeks after baseline, start of energy restriction; *t*_*6*_, 4 weeks in energy restriction; *t*_*10*_, 8 weeks in energy restriction; *t*_*14*_, 12 weeks in energy restriction; *t*_*18*_, 16 weeks in energy restriction; *t*_*26*_, 8 weeks in neutral energy balance; *t*_*78*_, 52 weeks in weight maintenance.

The study was approved by the Ethics Committee of the Faculty of Nutrition and Food Sciences, University of Porto (Approval Number 31/2021/CEFCNAUP/2021) and will be conducted in accordance to the declaration of Helsinki for human studies from the World Medical Association [33]. It has been registered at www.clinicaltrials.gov (NCT05184361) prior to participants’ recruitment.

All participants will be informed about the possible risks of this investigation before giving informed consent for enrollment in the study. Participants´ privacy and confidentiality will be ensured, during and after investigation, in accordance with the legislation in force.

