#### 3.5.1. Power sample calculation

For sample and power calculations, this study is powered based on changes in total body fat assessed by DXA. Considering a type I error of 5% and a power of 95% to detect differences at the dependent variable, with a statistical significance and an effect size of 0.93 (differences in FM (kg) were considered following Byrne et al. results [6]), a total of 26 participants per group will be needed (using GPower software version 3.1.9.6). Considering a 30% drop-out rate [6] throughout the study, we will recruit 74 participants (37 in each group).

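### Compound symmetry, the only named fallback for the covariance, would understate the standard error of the 12-month contrast if it is used and the women diverge over time

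*Protocol article*

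**What the plan says.** Section 3.5 fits one linear mixed model with group, time and their interaction, and lists baseline among the time levels. The repeated-measures covariance "will be modelled as unstructured or, if necessary, compound symmetry". The article does not say what makes the second choice necessary, and it names no structure between the two. The treatment comparison is a change-score contrast: "Difference-in-differences between IER and CER throughout time will be assessed by performing contrasts".

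The Fig 1 legend labels the visits as weeks 0, 2, 6, 10, 14, 18, 26 and 78, the last being "52 weeks in weight maintenance". Successive gaps are therefore 2, 4, 4, 4, 4, 8 and 52 weeks. Section 3 gives eight occasions for weight, bioimpedance and resting energy expenditure, and five for DXA. The Abstract makes change in fat mass and adaptive thermogenesis primary, both after weight loss and after weight maintenance.

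**The concern.** A difference-in-differences contrast takes its standard error from the variance of the change between two visits. Under compound symmetry that variance is one number for every pair of visits, whether 2 weeks or 18 months apart. Women who start close to their own baseline and then spend a year in free-living maintenance would be expected to spread out. One pooled variance is then too small for the longest contrast and too large for the shortest. The longest contrast is a primary one, so its interval would be too narrow and its false-positive rate above 5%.

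Adaptive thermogenesis raises a related difficulty. Putting baseline into the section 3.2.1 formula gives the baseline residual minus itself, which is zero for every woman. If baseline is kept as a time level for this outcome, that level has no variance, the unstructured matrix is singular, and the analyst is pushed towards the fallback.

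**Working it through.** **The plan's own figure.** The document gives no standard error, standard deviation over time or within-subject correlation, so there is no figure for this contrast to reproduce. The nearest is the sample size in section 3.5.1 (effect size 0.93, 5% error, 95% power): "a total of 26 participants per group will be needed". A one-sided calculation gives 2 × ((1.645 + 1.645)/0.93)² = 25.03, so 26. A two-sided one gives 2 × ((1.960 + 1.645)/0.93)² = 30.05, so 31. That difference is a separate matter. It does not enter here, because the ratio below does not depend on n.

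**Formula.** For complete balanced data with covariance matrix S:
- true variance of change from baseline to visit k = S₀₀ + Sₖₖ − 2S₀ₖ;
- variance under compound symmetry = 2 × (mean variance − mean covariance), the same for every k;
- SE ratio R = square root of (compound symmetry / true);
- actual size of a nominal 5% test ≈ 2Φ(−1.96R).

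**Inputs.** The visit weeks come from Fig 1. Every covariance pattern is an assumption.

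**Example A: correlation decays in calendar time, unit variance, correlation 0.8 between weeks 0 and 78.** The correlation is 0.8^(gap/78) and its mean over the 28 visit pairs is 0.9328. The compound-symmetry variance is 2 × (1 − 0.9328) = 0.1345 up to rounding.

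| Contrast with baseline | True variance of change | R | Actual size |
|---|---|---|---|
| Week 2 | 2(1 − 0.9943) = 0.0114 | 3.43 | near 0 |
| Week 18 | 2(1 − 0.9498) = 0.1004 | 1.16 | 2.3% |
| Week 78 | 2(1 − 0.8) = 0.4 | 0.58 | 26% |

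**Example B: first-order autoregressive by visit order, 0.90.** The mean covariance is 0.7408, so the compound-symmetry variance is 2(1 − 0.7408) = 0.518.
- Week 2: true 2(1 − 0.9) = 0.2, R = 1.61.
- Week 18: true 2(1 − 0.9⁵) = 0.819, R = 0.80.
- Week 78: true 2(1 − 0.9⁷) = 1.043, R = 0.70, size 17%.

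The week-18 error has the opposite sign to that in Example A.

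**Range for the 12-month contrast.**

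| Assumed pattern | R |
|---|---|
| Eight visits, calendar-time decay, r(0,78) from 0.3 to 0.9 | 0.57–0.63 |
| Same, with 5–10% measurement-error variance | 0.66–0.82 |
| Same decay, SD growing 20–40% by week 78 | 0.55–0.58 |
| Autoregressive by visit, 0.80–0.95 | 0.68–0.76 |
| Random intercept and slope | 0.81 |
| Five DXA visits (weeks assumed), all patterns | 0.65–0.86 |
| Compound symmetry true | 1.00 |

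The extremes are:
- Low end: SD growing 40% with correlation 0.8. Mean variance 1.2218 and mean covariance 1.1144 give 0.2149. The true value is 1 + 1.96 − 2 × 1.4 × 0.8 = 0.72, so R = 0.55 and the size is 28%.
- High end: four visits (weeks 0, 18, 26, 78), 10% measurement error, correlation 0.8. The mean covariance of 0.847 gives 0.305 against 0.4, so R = 0.87 and the size is 9%.

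Hence R runs from 0.55 to 0.87, an SE that is 45% to 13% too small. Using the longer IER calendar gives similar ratios. At week 2, R is 1.08 to 4.3. At week 18 it is 1.04 to 1.35 under calendar-time decay or a random slope, and 0.78 to 0.82 under autoregression by visit. Dropout was not modelled.

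**In kilograms.** Assume SDs of fat-mass change of 1.2 kg at 4 weeks of restriction, 3.5 kg at 16 weeks and 6 kg at 12 months. Compound symmetry then implies one SD of 3.7 kg (eight visits) to 4.2 kg (five visits). With 26 per arm the true 12-month SE is 6 × √(2/26) = 1.66 kg, against a reported 1.03 to 1.16 kg.

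**Parameters.** Unstructured needs 8 × 9/2 = 36 for eight visits and 5 × 6/2 = 15 for five. Compound symmetry needs 2.

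**The case against.** The strongest reply is that the fallback may never be used. Unstructured is the stated first choice. The powered outcome, DXA fat mass, needs only 15 parameters. Under intention-to-treat all 74 women contribute the visits they attended, each giving up to eight values. In a simulation with 37 per arm, eight visits, 22 of 74 dropping out, 5% intermittent missing values and an assumed growing spread, 60 of 60 unstructured fits converged to a positive-definite matrix (not run in SPSS). This stands: a reader might infer that the fallback is likely, and the document does not support that.

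Three further limits also stand.
- A reader might take a figure such as a one-third shortfall as established. It is one point in an assumption-based range that includes zero if compound symmetry is true.
- A reader might infer that all contrasts before 12 months are too conservative. That is safe only for the first visits.
- The zero baseline for adaptive thermogenesis does not single out compound symmetry, since heterogeneous structures also need a positive variance at each level. Nor does section 3.5 say that this outcome is entered with a baseline level; it describes one generic model.

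It can also be said that convergence rules belong in an analysis plan that is not shown. That is fair for the trigger and for intermediate structures. It does not cover the fallback itself, which the article chooses and names.

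**Conclusion.** The point holds as a conditional one. If compound symmetry replaces unstructured, and correlation decays or spread grows over visits 2 to 52 weeks apart, the standard error of a primary 12-month contrast is too small. That direction was the same in every departure from compound symmetry that was tried. The size, 13% to 45% with an actual test level of about 9% to 28%, depends on patterns the document does not supply, and on complete data. No direction can be claimed for the end-of-restriction contrast. The probability that the fallback is invoked is unknown; it is lower for DXA fat mass than for the eight-visit outcomes.

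**What to change.** - Keep unstructured as the first choice, and delete compound symmetry as the fallback.
- Pre-specify an ordered replacement, used only if unstructured fails to converge: for example heterogeneous Toeplitz, then heterogeneous first-order autoregressive, with Kenward-Roger or Satterthwaite degrees of freedom. For eight visits these need 8 + 7 = 15 and 8 + 1 = 9 parameters. Both give each visit its own variance. In the Toeplitz form the baseline-to-week-78 pair is the only one at the longest lag, so its correlation is not tied to the others.
- For adaptive thermogenesis, leave baseline out as a time level; values at later visits are already changes from baseline. Alternatively, model measured minus predicted resting energy expenditure with baseline included. Without one of these, unstructured and heterogeneous structures are singular for this outcome.
- Do not make a separate ANCOVA at each visit the routine fallback. It discards the post-baseline data of women who drop out, and section 3.5.1 plans for 30% dropout.

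The cost is a change of wording in the analysis section, and slightly wider 12-month intervals if the fallback is used. If unstructured converges, the covariance results do not change.

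### Comparing arms by change from a freely estimated baseline is valid, but less precise than adjusting for the t0 value that the trial already collects

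*Protocol article*

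**What the plan says.** Section 3.5 of the protocol article specifies linear mixed models with fixed effects for group, time and group by time. The levels of time include the baseline visit, the start of energy restriction, the four-weekly visits and the later phases. The between-arm comparison is then written out: "Difference-in-differences between IER and CER throughout time will be assessed by performing contrasts", with the change from a time 1 to a time 2 in CER subtracted from the same change in IER. No constraint on the baseline means is stated, and the baseline value is not named as a covariate. On covariates in general, the text says "When necessary, adjustments for confounding variables (covariates) will be considered".

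Section 3.2.1 defines AT as measured minus predicted REE at the later time, less the same difference at baseline. It is thus the change in a residual from one baseline measurement. FM loss and AT are both primary outcomes, but section 3.5.1 states that "this study is powered based on changes in total body fat assessed by DXA".

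Two visits precede restriction: t0, and t2, which the Fig 1 legend describes as "2 weeks after baseline, start of energy restriction". Section 2.4 places randomisation before the first visit and disclosure of the arm during it.

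**The concern.** Randomisation gives both arms the same expected value at t0. A model that estimates a separate t0 mean for each arm, and then subtracts it, does not use that knowledge. It removes the whole of the observed baseline difference, although only a fraction of it is expected to persist to follow-up. The rest of the subtraction adds noise.

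This matters most where the signal is small and the baseline is measured with error. The Introduction reports AT of about 209 kJ/d (209/4.184 = about 50 kcal/d) in the cited trial, in its continuous arm only. In this trial AT is a primary outcome without a power calculation of its own, and each AT value carries the error of one baseline calorimetry.

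**Working it through.** **Inputs.** The model and contrast are from section 3.5, the AT formula from section 3.2.1, the effect size of 0.93 and the sample size from section 3.5.1, and the timing of randomisation from section 2.4. The correlation r between baseline and follow-up is an assumption, shown over a range.

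**1. The plan's own sample size.** Section 3.5.1 says "a total of 26 participants per group will be needed" for an effect size of 0.93, type I error 5% and power 95%. A two-sample t-test (noncentral t) gives 26 per arm, with power 95.2%, if one-sided. Two-sided, as section 3.5 sets the tests, it needs 32 per arm, and 26 per arm has 90.8% power. Sidedness is a separate matter; 32 and 90.8% are the two-sided reference values below.

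**2. Precision of the two estimators.** With complete data, equal variances and unit variance per visit:

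- planned change score: Var(Y_t − Y_0) = 2(1 − r)
- adjusted for, or constrained at, t0: 1 − r²
- ratio: (1 − r)(1 + r) / [2(1 − r)] = (1 + r)/2

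| r | 2(1−r) | 1−r² | Ratio | SE reduction | n per arm for 95% power | Power at 26 per arm |
|---|---|---|---|---|---|---|
| 0.9 | 0.20 | 0.19 | 0.95 | 2.5% | 30 | 92.1% |
| 0.7 | 0.60 | 0.51 | 0.85 | 7.8% | 27 | 94.6% |
| 0.5 | 1.00 | 0.75 | 0.75 | 13.4% | 24 | 96.7% |
| 0.3 | 1.40 | 0.91 | 0.65 | 19.4% | 21 | 98.3% |

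The SE reduction is 1 − √ratio. The last two columns are two-sided and assume that 0.93 is the standardised effect on the change in fat mass; the effect size becomes 0.93/√ratio. A generalised least squares calculation with eight visits and compound symmetry gave the same four ratios.

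**3. Two checks on the formula.** If the variances differ, the planned variance minus the adjusted variance is σ_0² + σ_t² − 2rσ_0σ_t − σ_t²(1 − r²) = (σ_0 − rσ_t)². This is never negative, and it is zero only if the regression slope on baseline is exactly 1. Estimating that slope costs a factor of about 1 + 1/(2n − 4), which is 1 + 1/48 = 1.021 at 26 per arm. At r = 0.9 the ratio becomes 0.95 × 1.021 = 0.97. The table leaves this factor out.

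**4. AT.** Write R = mREE − pREE. Then AT at visit t is R_t − R_0, and the arm difference in AT is the difference-in-differences of R, so step 2 applies with r taken for R. AT at t0 is R_0 − R_0 = 0 for every participant. If AT itself is the outcome, its baseline value cannot serve as a covariate. If the t0 level is kept in the model, it has no variance and an unstructured covariance matrix is singular.

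**5. A second baseline at t2.** Adjusting for the mean of t0 and t2, whose correlation with each other is b, gives variance 1 − 2r²/(1 + b). At r = 0.7:

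- b = 0.70: 1 − 0.98/1.70 = 0.424; ratio 0.424/0.60 = 0.71
- b = 0.85: 1 − 0.98/1.85 = 0.470; ratio 0.470/0.60 = 0.78

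**The case against.** The strongest reply is that difference-in-differences is a standard estimator and unbiased over randomisation. Nothing here shows bias, an inflated type I error or a contradiction. For fat mass, the powered outcome, r may well be high, and at r = 0.9 the saving is about 5% of the variance or less. All of this stands.

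Several stronger readings are tempting, and the document does not support them:

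- A reader might infer that the analysis is unadjusted. Covariate adjustment is allowed; what is not fixed is adjustment for baseline. The list of other covariates and their trigger are details that a SAP commonly holds, so their absence is not part of this point.
- A reader might infer that the plan overlooks its two visits before restriction. Both are levels of the time factor in section 3.5.
- A reader might infer that AT suffers most. That needs a lower r for the REE residual than for fat mass. This is plausible for a residual, but no correlation is given for either.
- A reader might take t2 as a free second baseline, worth about 40% more participants (1/0.71 = 1.41). That figure assumes that t0 and t2 correlate with each other no more closely than with later visits. At b = 0.85 it is about 28% (1/0.78 = 1.28). More importantly, the arm is known from the first visit, so randomisation alone does not guarantee equal means at t2. For fat mass, the text does not show DXA at both visits: section 3 gives five scans, and their timing is only in Fig 2, which is not shown.

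**Conclusion.** The concern holds as a loss of efficiency. The plan writes out its contrast, and that contrast is less precise than adjustment for a t0 value already collected. The saving in variance is 5% at r = 0.9, 15% at 0.7, 25% at 0.5 and 35% at 0.3, before the small cost of estimating the slope. These figures rest on complete data, equal variances and an assumed r. They are modest for fat mass if r is high, and larger for AT only if its residual correlates less strongly over time. The planned estimate remains valid; only precision, and with it sensitivity to chance baseline imbalance in a single trial, is at stake. The change is worth making because it costs nothing and AT was not powered.

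**What to change.** - **All outcomes:** keep the mixed model, but constrain the arm means to be equal at t0, with arm by time effects from later visits. Alternatively, use ANCOVA with the t0 value of the outcome as a pre-specified covariate. Randomisation precedes t0, which supports this. The accelerometer is worn for seven days after the visit (section 3.3), so for outcomes based on it the t0 constraint also assumes no effect of knowing the arm.
- **AT:** model the residual mREE − pREE at t0 and at each visit where FM and FFM come from one consistent method, with the t0 residual constrained or adjusted for. Section 3.2.1 does not say whether DXA or BIA supplies FM and FFM, so this needs stating. AT can still be reported descriptively.
- **t2:** use it as a second baseline only in an optional sensitivity analysis of REE-based outcomes, and state the assumption that disclosure of the arm had no effect by then.

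The cost is analysis wording. No new data, visits or software are needed.

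### Single imputation from demographics and baseline measures is not a valid check on the mixed model, although the primary analysis itself is unaffected

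*Protocol article*

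**What the plan says.** Section 3.5 of the protocol article sets the main analysis: "Linear mixed models will be used to assess outcomes for the impact of group, time and group*time interaction". Time covers the visits from baseline to the end of weight maintenance, and the within-subject covariance is unstructured or, if needed, compound symmetry. On the analysis set it says "All analysis will be intention-to-treat, including data from all the participants who will assign in this study". The test level is two-sided 5%.

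On missing data, the same section says "Sensitivity analyses will be carried out for some variables of interest", and specifies how: "by using single imputation of missing data to predict missing outcomes from demographics and baseline measures". Randomized arm and post-baseline measurements are not listed as predictors. The section does not say whether a random residual is added to the predicted values, and it mentions no multiple imputation or variance correction.

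Section 3.5.1 takes an effect size of 0.93 for fat mass, 26 evaluable women per group and, "Considering a 30% drop-out rate" over the whole study, 37 recruited per group. Section 3 gives 8 visits with weight, body composition and REE, and 5 with DXA.

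**The concern.** A sensitivity analysis for missing data should ask whether the main conclusion survives a different, credible treatment of the missing values, with honest uncertainty. This one has three weaknesses.

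- If arm is not in the imputation model, the imputed values carry no between-arm difference beyond chance imbalance at baseline, so the estimate is diluted by the share imputed.
- If arm is in the model, the dilution goes, but predicted values are analysed as if measured and the standard error is too small.
- In both cases the course of each woman up to drop-out is discarded. The mixed model uses it, so the check has less information than the analysis it checks.

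At stake is how the robustness statement will be read. A disagreement with the mixed model could be produced by the imputation method alone. If arm is included, an apparent confirmation could reflect understated uncertainty.

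**Working it through.** **Inputs from the documents.** 37 recruited and 26 evaluable per group, 30% drop-out and effect size 0.93 (section 3.5.1); two-sided 5% level (section 3.5); 1:1 allocation (section 2.1).

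**Inputs assumed.** Values missing completely at random, equal drop-out by arm, drop-outs sharing the true effect, and a baseline R-squared for the change, which the article does not give and which is varied below.

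**The plan's own figures.** 37 × 0.7 = 25.9, so 26 are observed and 37 − 26 = 11 imputed per arm; the imputed share is f = 11/37 = 0.297. The 26 per group for 0.93 and 95% power reproduces with a one-sided 5% test (power 95.2%); a two-sided t-test needs 32. That is a separate matter. Only the 26/37 split is used here.

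**Step 1: arm not a predictor (literal reading).** Both arms get the same expected imputed value, so the completed-data difference is (26 × δ + 11 × 0)/37 = 0.703 δ. With δ = 0.93 this is 0.65, about 30% smaller, whatever the baseline R-squared. Simulated mean estimates were 0.64 to 0.66, with type I error between 0.046 and 0.053.

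**Step 2: arm a predictor, no random residual, R-squared 0.** In units of the outcome variance:
- variance the analysis reports: (26/37) × (2/37) = 0.0380
- true variance: 2/26 = 0.0769
- SE ratio: √(0.0380/0.0769) = 0.703
- the test in effect rejects at |z| > 1.96 × 0.703 = 1.38, so type I error is 0.168.

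**Step 3: arm a predictor, random residual added, R-squared 0.**
- variance reported: 2/37 = 0.0541
- true variance: 2/26 + (11/37)² × (2/11) = 0.0769 + 0.0161 = 0.0930
- SE ratio: √(0.0541/0.0930) = 0.762
- rejection at |z| > 1.49, so type I error is 0.135.

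**Step 4: how far this depends on R-squared.** Write R for R-squared. For an unadjusted analysis of change without a residual, the reported variance is [R + (1 − R)(1 − f)] × 2/37 and the true variance is R × 2/37 + (1 − R) × 2/26. With a residual, the reported variance is 2/37 and the true variance gains (1 − R) × f² × 2/11.

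| Baseline R-squared | No residual | With residual |
|---|---|---|
| 0 | 0.168 | 0.135 |
| 0.2 | 0.139 | 0.118 |
| 0.5 | 0.100 | 0.093 |

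In simulations adjusted for baseline, R-squared made little difference: 0.171 to 0.176 without a residual and 0.133 to 0.141 with one.

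**Step 5: fewer missing values.** Arm a predictor, no residual, R-squared 0. The shares below 30% are illustrative, since the article gives no drop-out by visit.

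| Imputed per arm | Share | Shrinkage if arm omitted | Type I error if arm included |
|---|---|---|---|
| 4 of 37 | 11% | 11% | 0.080 |
| 7 of 37 | 19% | 19% | 0.112 |
| 9 of 37 | 24% | 24% | 0.138 |
| 11 of 37 | 30% | 30% | 0.168 |

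The simulations used 10,000 runs per type I error and 4,000 per effect estimate. They compared two arms at one visit on the completed data; they did not refit the full mixed model.

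**The case against.** The strongest reply is that this is only a sensitivity analysis, for some variables. The mixed model uses all observed data, handles drop-out under missing at random and takes nothing from the imputation. That stands. A reader might infer that the trial's primary estimates are biased or that its error rate is inflated; the documents do not support either.

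A reader might also infer that the plan as written raises the false-positive rate two- to threefold. It does not: the article lists only demographics and baseline measures, and on that reading type I error stays near 5%. The inflation needs an arm term that the text does not state.

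Third, leaving arm out could be defended as a deliberately conservative stress test, since it departs from the mixed model's assumption in the direction of no difference. In part this is fair: the 30% is a bias only if drop-outs keep the true effect. But the article does not present it as such a scenario, and it would be an odd one. With equal numbers observed, the common imputed mean lies halfway between the arms, so CER drop-outs are credited with half of any IER advantage.

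Fourth, the 30% is drop-out over the whole study and so bears on the last visit; fat mass at the end of energy restriction should be less affected. That also stands.

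Finally, a condensed article may leave imputation details to a full plan. But the two features that cause the trouble, single imputation and baseline-only predictors, are stated. The absence of a delta-adjusted analysis is not an error.

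**Conclusion.** The concern holds for the sensitivity analysis alone. As stated, it is diluted towards no difference: about 30% at the last visit, 0.93 falling to about 0.65, with type I error near 5%. If arm is added, the estimate is unbiased but the two-sided type I error is about 13-17% when baseline explains little of the change or the analysis is baseline-adjusted. It is about 9-10% at an R-squared of 0.5 unadjusted, and lower at visits with fewer missing values. These sizes rest on 30% missing, missingness completely at random and equal drop-out by arm; the dilution also assumes that drop-outs share the true effect. Neither version is a sound check on the mixed model, and both ignore post-baseline data. The point should be fixed before analysis, but it does not threaten the primary analysis.

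**What to change.** Replace the single imputation in section 3.5 with multiple imputation, for example 50 data sets combined by Rubin's rules. The imputation model should include randomized arm, baseline and earlier values of the same outcome, plus at most one auxiliary such as the latest weight.

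Keep it sparse. If the last visit includes DXA, entering every earlier weight, REE, FM and FFM value would mean 7 + 7 + 4 + 4 = 22 predictors against about 26 completers per arm. Weight, FM and FFM should not enter together, because FM plus FFM is close to weight.

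A delta-adjusted scenario, with drop-outs assumed to do progressively worse than predicted, is an optional addition.

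The cost is a little more analysis work and wider, honest confidence intervals in the sensitivity analysis. The named software can do it, and no new data, visits or participants are needed.
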